### Statistical analysis and sample size

The primary analysis will be by intention-to-treat (ITT). Per-protocol analyses will also be performed, based on all patients completing 1, 6 and 12 months follow-up. Based on our prospective study [16], comparing routine care with the formalised TTS group, we anticipate a decrease in post discharge (Type III) injuries from 14% to 9%. We foresee this will be accompanied by an increase of in-hospital injury detection (missed injury Type I and II combined) from 4% to 9%.

The sample size for a cluster-randomized trial requires adjustment of the number of patients that a corresponding individually randomized trial would have needed. This is due to variation between the clusters, and results in a correction using the intra-cluster correlation coefficient (ICC) [21]. Using an alpha of 0.05 and a power of 0.80, a sample size of 638 patients per group, with 1-year follow-up completed, would be required if individually randomised. Our previous study [17] achieved a telephone follow-up rate of 40% at 6 months. Extrapolating a similar conservative follow-up rate at 12 months, a total of 3,190 patients will be required (1,595 for each cohort) to answer the primary hypothesis. To separately answer a before-and-after comparison in Group 2 hospitals a similar sample is required. This results in a sample of 6,380 patients, with complete 1-year follow-up in at least 2,552. Since approximately 0.4% [22] of all ED presentations consist of multi-trauma patients, approximately 1,600,000 ED presentations will be required. For an approximate 24-month recruitment period, this equates to 16 hospitals that have an average annual census of 50,000 presentations. Based on this sample size, the maximum ICC that can be present before the power of the study is reduced below 80% is dependent on cluster size and numbers and presented in Table 3*.*

**Table 3 Tab3:** **Approximate maximum intra-class correlation (ICC) for various cluster sizes and number of intervention hospitals to answer primary hypothesis**

**Number of intervention (and control) hospitals**	**Average size of cluster**	**Maximum ICC to have 80% power to detect 5% difference**
8	400	0.01
15	400	0.02
21	400	0.03
9	300	0.01
15	300	0.02
22	300	0.03
10	200	0.01
16	200	0.02
23	200	0.03

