This calculation is consistent with a previous study specifically examining the ICC in trauma receiving hospitals. ICC varied depending on outcome, but the average ICC for blunt trauma the ICC was 0.01 [23]. Assuming an average cluster size of 250 patients, this would mean a total of 3,440 patients would require recruitment (approximately 14 clusters) for the primary hypothesis.

The study is adequately powered for the primary hypothesis, and for several secondary outcomes, such as pre- and post-comparison in Group 2, but not for the pre- and post- comparison in Group 1, measuring maintenance of the intervention effect.

De-identified data will be analysed using SPSS v20.0 software (SPPS Inc, Chicago, IL, USA). For continuous variables, we will use an independent *t*-test and chi-square test will be used to compare differences in proportions. All results will be presented with 95% confidence intervals.

Health economic analyses will include a within trial incremental cost-effectiveness evaluation of formal TTS versus standard care. The outcome measure, incremental cost-effectiveness ratio, directly compares the difference in costs between the formal TTS and standard care with the difference in health related quality of life. Health-related quality of life will be measured in quality adjusted life years (QALYs) derived from changes in EQ-5D-5 L measured at multiple time points. A cost-effective threshold of $AUD 50,000 per QALY will be used to determine whether the intervention was cost-effective and a cost-effectiveness acceptability analysis will be conducted using a range of threshold values from $20,000 to $100,000. A 95% confidence interval around the incremental cost-effectiveness ratio will be estimated using bias-adjusted bootstrapping. In addition, sensitivity analyses and sub-group analyses will be conducted to identify the parameters and patient characteristics that affect the likelihood of the intervention being cost-effective. A *P* value of 0.05 or less will be deemed statistically significant.

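### The 6,380 total contains no allowance for clustering, and Table 3 assumes 400 analysed patients per hospital where the primary comparison has about 80; at ICC 0.01 power is about 50–56%, not 80%

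*Protocol article*

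**What the plan says.** All of this is in the Protocol article, Statistical analysis and sample size.

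- The section states that a cluster-randomised trial needs its sample size corrected through the ICC.
- The starting point is the Type III rate: "we anticipate a decrease in post discharge (Type III) injuries from 14% to 9"%. At alpha 0.05 and 80% power this gives "a sample size of 638 patients per group, with 1-year follow-up completed, would be required if individually randomised".
- The earlier study "achieved a telephone follow-up rate of 40% at 6 months", and the same rate is assumed at 12 months. Hence "a total of 3,190 patients will be required (1,595 for each cohort) to answer the primary hypothesis".
- A further 3,190 is added for the before-and-after comparison within Group 2 hospitals. The total is 6,380, with 2,552 completers, in 16 hospitals over 24 months.
- Table 3, introduced as resting on this sample size, has a column headed "Maximum ICC to have 80% power to detect 5% difference". Its first row is 8 hospitals per arm, average cluster size 400, maximum ICC 0.01.
- The text after the table cites an average ICC of 0.01 for blunt trauma and gives 3,440 patients in about 14 clusters of 250 for the primary hypothesis. It then concludes: "The study is adequately powered for the primary hypothesis, and for several secondary outcomes, such as pre- and post-comparison in Group 2".

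**The concern.** The section announces a correction for clustering, but its arithmetic goes from the individually randomised number to the final total without one. Table 3 is then the only link between the planned sample and the 80% claim, and its cluster sizes do not match what the primary comparison will contain. The 400 per hospital is close to the whole 24-month enrolment per hospital. The primary contrast uses only the first 12 months, because Group 2 hospitals start the intervention after that, and only about 40% of patients are expected to complete follow-up.

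The Discussion says that if the survey is not shown to be effective, it should be abandoned where it is already partly in use. A trial with roughly even odds of missing the effect it was designed to find could not support that conclusion from a null result.

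**Working it through.** **Inputs (all from the protocol).** Rates 14% and 9%; alpha 0.05 (two-sided reproduces the stated figure); power 80%; follow-up 40%; 16 hospitals, 8 per arm; ICC 0.01; randomised comparison confined to the first 12 months. Equal cluster sizes are assumed.

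**1. Reproducing the plan's totals.** The pooled two-proportion formula is

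n = [1.96·√(2·0.115·0.885) + 0.8416·√(0.14·0.86 + 0.09·0.91)]² / 0.05² = 637.9, so 638 per group.

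- 638 / 0.40 = 1,595 per arm
- 2 × 1,595 = 3,190
- 2 × 3,190 = 6,380
- 0.40 × 6,380 = 2,552 completers

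Every step is exact, so the inflation for clustering is 1.0.

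**2. What Table 3 assumes.** With k hospitals per arm, m patients per hospital and design effect 1 + (m − 1)·ICC, the effective sample per arm is k·m / [1 + (m − 1)·ICC].

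| k | m | ICC | Effective n per arm |
|---|---|---|---|
| 8 | 400 | 0.01 | 641 |
| 15 | 400 | 0.02 | 668 |
| 21 | 400 | 0.03 | 648 |
| 9 | 300 | 0.01 | 677 |
| 15 | 300 | 0.02 | 645 |
| 22 | 300 | 0.03 | 662 |
| 10 | 200 | 0.01 | 669 |
| 16 | 200 | 0.02 | 643 |
| 23 | 200 | 0.03 | 660 |

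Every row just exceeds 638, so the table counts m as patients analysed in the primary comparison, with no loss to follow-up. The first row therefore means 8 × 400 = 3,200 analysed per arm. At 40% follow-up that is 2 × 3,200 / 0.40 = 16,000 enrolled in the first year.

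**3. What the plan supplies.** 6,380 / 16 = 399 enrolled per hospital over 24 months. For the primary comparison, 3,190 / 16 = 199 enrolled per hospital, and 0.40 × 199 ≈ 80 completers.

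Maximum ICC for 80% power at 8 hospitals of 80: (640/638 − 1) / 79 = 0.00004.

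**4. Power with 8 + 8 hospitals of 80 completers.** At ICC 0.01 the design effect is 1 + 79 × 0.01 = 1.79, and the effective n is 640 / 1.79 = 357.5 per arm. The standard error is √[(0.1204 + 0.0819) × 1.79 / 640] = 0.0238. Then 0.05 / 0.0238 = 2.10, and power = Φ(2.10 − 1.96) = 0.556 (0.554 with the pooled-variance form). A noncentral t with 2 × 8 − 2 = 14 df gives 0.499.

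| ICC | Power, normal (pooled-variance) | Power, t (14 df) |
|---|---|---|
| 0.001 | 77% | 71% |
| 0.002 | 74% | 68% |
| 0.005 | 66% | 60% |
| 0.01 | 55% | 50% |
| 0.02 | 42% | 37% |
| 0.03 | 33% | 30% |

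At ICC 0.01 the difference detectable with 80% power from a 14% control rate is about 6.5 points (normal) or 6.9 points (t).

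**5. More generous readings, ICC 0.01, 8 hospitals per arm.**

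| Analysed per hospital | Reading | Power, normal | Power, t |
|---|---|---|---|
| 120 | 60% follow-up | 64% | 58% |
| 160 | completers from both years | 69% | 63% |
| 200 | all first-year patients | 73% | 67% |

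None reaches 80%.

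**6. The 3,440 figure.** At m = 250 and ICC 0.01 the design effect is 1 + 249 × 0.01 = 3.49. The requirement is 2 × 638 × 3.49 = 4,453 analysed, or about 11,133 enrolled at 40% follow-up. Fourteen clusters of 250 give 70% power with everyone followed, and about 55% with 100 completers each (normal). The 3,440 does not follow from its inputs, and it also exceeds the 3,190 allotted to the primary hypothesis.

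**The case against.** The strongest counter-arguments concern how firmly the 50–56% can be stated.

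- **The ICC is uncertain.** The protocol cites 0.01 as an average for blunt trauma and says that the ICC varied by outcome; it is not an ICC for Type III missed injury. That stands, and the figure should always carry its ICC. Lower values help but do not rescue the claim: power is 74% at 0.002 and 66% at 0.005 (normal).
- **Table 3 does not say whether cluster size means enrolled or analysed, and the primary analysis is intention-to-treat.** If all of roughly 200 first-year patients per hospital were analysed, the tolerable ICC would be (1,600/638 − 1) / 199 = 0.0076, not zero. That is still below 0.01. The section sizes its 638 on patients with one-year follow-up completed, so the completer reading is better supported.
- **Forty per cent may be pessimistic for this outcome.** The 14% control rate resembles the one-month figure in the Background (13.7%), while the 40% is a six-month follow-up rate. Earlier reports could raise the number contributing. No one-month follow-up rate is given, and even complete follow-up leaves power at 73%.
- **Clustering is not concealed.** The section says that 638 applies to individual randomisation and makes 80% power conditional on a maximum ICC. That is fair. The error lies in the mismatched table inputs and the unconditional adequacy statement.
- **The quoted sentence also covers the Group 2 before-and-after comparison.** Its power needs a between-period correlation within hospitals, which the protocol does not give, so nothing is shown here about that part.

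**Conclusion.** The concern holds. The 3,190 and 6,380 contain no design effect, and Table 3 describes a trial with five times as many analysed patients per hospital (400 against 80) as the primary comparison will have. With 16 hospitals, 80 first-year completers each and ICC 0.01, power for 14% versus 9% is about 50–56%, and the detectable difference is about 6.5 to 7 points. With 80 completers per hospital, the 80% claim holds only at an ICC of essentially zero. No reading of follow-up or pooling examined restores it at ICC 0.01.

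The result rests on the protocol's rates, its 40% follow-up, its cited ICC and equal cluster sizes; unequal sizes would lower power further. This must be corrected before the trial starts.

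**What to change.** 1. Withdraw the statement of adequate power as it applies to the primary hypothesis. For the Group 2 before-and-after comparison, either give a calculation with a stated between-period correlation or make no power claim.
2. State that with 16 hospitals and about 80 first-year completers per hospital, power for 14% versus 9% is about 50–56% at ICC 0.01, with a detectable difference of about 6.5 to 7 points. Show a range of ICCs on both sides of 0.01.
3. Rebuild Table 3 on completers per hospital per 12-month period (40% of first-year enrolment), label the column accordingly, and include the row that matches the plan: 8 hospitals per arm, 80 completers, maximum ICC about 0.
4. Correct or remove the 3,440 figure, so that it does not sit beside a table it contradicts.

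The cost is restated text and a less favourable power figure; recruitment had not begun when the article was written. If the sponsor wants to keep 80% at ICC 0.01, 638 × 1.79 = 1,142 completers per arm are needed. At 80 per hospital that is 14.3, so 15 hospitals per arm (82% normal, 79% with t). The primary comparison alone would then need 2 × 1,142 / 0.40 ≈ 5,710 enrolled, or 2 × 15 × 80 / 0.40 = 6,000 with whole hospitals.

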**Table 2 Tab2:** **Data Collection**

***Time***	***Data collection process***
Enrolment	A trained research assistant will prospectively review (electronic) medical records for details on all clinical examinations, pathology tests and diagnostic imaging performed in the first 24 hours of admission. A standardised data collection form will be used for all patients. This review will occur between 24 and 48 hours after initial admission. This data is routinely collected data and as such, patient will not be asked to consent to this.
Enrolment	The patient or proxy will be asked to consent for the follow-up at 1, 6 and 12 months. The patient or proxy will be asked to provide at least two contact numbers and will be informed on the detail of these follow up interviews.
Follow-up	Structured interview at 1, 6 and 12 months after hospital discharge. A list of self-reported missed injuries will be adjudicated by an expert panel to classify the in-hospital missed injury (none, Type I or II) and any Type III injury as definite or likely, as well as to determine clinical significance of any missed injury
Follow-up	A trained research assistant will conduct a scripted follow-up interview that will include questions on delayed diagnosis or missed injuries, level of functioning, time off work and quality of life
	*Study measurements*
	Age
	Sex
	Ethnicity
	Occupation
	ISS score.
	Length of Hospital stay, length of ICU stay
	TTS performance and components of TTS (Additional file 1: Appendix A)
	Diagnoses made after 24 hours in hospital, resultant management (active or conservative), diagnostic procedures or tests.
	Predefined complications of care: post-operative infection (wound infection, cathether-related urinary tract infection, pneumonia, sepsis), and venous thrombo-embolism (Deep Vein Thrombosis, Pulmonary embolism)
	Predefined complications of injury: (ongoing or chronic pain, parasthesia, post-concussion syndrome or symptoms)
	Numbers of CT, MRI and ultrasound scans performed
	Details of unplanned attendances and readmissions to hospital
	Patient quality of life at 1, 6, 12 months (EQ-5D-5 L)
	Proportion of usual days of work or study lost at 1, 6 and 12 months
	Missed injury after hospital discharge
	Medical and nursing time used to assess patients in the first 24 hours
	ICD-10 diagnostic and procedure codes
	Australian-Revised Diagnostic-Related Group (AR-DRG) codes
	Community medical services provided

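### EQ-5D-5L and work time lost are collected three times with heavy loss expected, but the stated t-test leaves a later-visit comparison without the earlier answers of patients since lost

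*Protocol article*

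**What the plan says.** The section on statistical analysis and sample size gives one rule for all continuous outcomes: "For continuous variables, we will use an independent" t-test. Outside the health-economic analysis no other method is named for them.

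Table 2 lists "Patient quality of life at 1, 6, 12 months (EQ-5D-5 L") and "Proportion of usual days of work or study lost at 1, 6 and 12 months". Both are secondary outcomes, and the aims name better quality of life and less time off work as hypothesised benefits.

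On follow-up, the authors' earlier study "achieved a telephone follow-up rate of 40% at 6 months", and the sample size rests on "Extrapolating a similar conservative follow-up rate at 12 months".

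On analysis sets: "The primary analysis will be by intention-to-treat (ITT"). In addition, "Per-protocol analyses will also be performed, based on all patients completing 1, 6 and 12 months follow-up". The article does not say at which visit the t-test is applied, or how a patient with a missing visit enters the intention-to-treat analysis. The only analysis described as combining the EQ-5D time points is the QALY derivation for cost-effectiveness.

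**The concern.** A two-sample t-test at 12 months compares only the patients interviewed at 12 months. A patient who answered at 1 month and was then lost contributes nothing to it, although the 1-month score is likely to predict the 12-month score and may predict who is lost. With about 60% loss planned at 12 months, this could affect many patients.

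Two things are at stake. Information already collected goes unused, so the interval for the arm difference is wider than necessary. The comparison is also exposed if recovery drives loss to follow-up differently in the two arms, or if the arms already differ at 1 month. The completers-only set is no safeguard, because it drops partial responders altogether.

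**Working it through.** **1. The plan's own figures.** Inputs from the sample size text: 14% versus 9%, alpha 0.05 (two-sided), power 0.80, 40% follow-up. With pooled variance under the null (mean rate 0.115):

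n = [1.96·√(2·0.115·0.885) + 0.8416·√(0.14·0.86 + 0.09·0.91)]² / 0.05² = (0.884 + 0.379)² / 0.0025 ≈ 638 per group.

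This agrees with "Using an alpha of 0.05 and a power of 0.80, a sample size of 638 patients per group". Then 638/0.40 = 1,595 per cohort, 2 × 1,595 = 3,190, 2 × 3,190 = 6,380, and 0.40 × 6,380 = 2,552, all as stated. So the plan expects about 638 of 1,595 per arm at 12 months. A 12-month t-test uses nothing from the other 957, whoever among them was interviewed earlier.

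**2. Assumptions not in the documents.** Correlation between 1- and 12-month scores ρ = 0.6; EQ-5D SD 0.25; share reached at 1 month p₁ from 42% to 80%; hospital clustering ignored. Follow-up at 6 and 12 months is planned at the same rate, so what matters is how much loss falls after the 1-month interview. That is why p₁ is shown as a range.

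**3. Precision when loss is random.** Using the 1-month score, the variance of an arm's 12-month mean is multiplied by 1 − ρ²(1 − 0.40/p₁). The t-test SE is therefore larger by the factor 1/√[1 − 0.36(1 − 0.40/p₁)].

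**4. Bias when drop-out depends on the 1-month score.** Let retention after the 1-month interview average r = 0.40/p₁ and follow a logistic curve in the standardised 1-month score. Let m be the mean of that score among patients retained. The t-test shifts each arm's 12-month mean by ρ·SD·m = 0.15·m, so the arm difference is shifted by 0.15·(m in one arm − m in the other). With slope 0.5 per SD in one arm, 1.0 in the other, and the same 1-month distribution in both:

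| p₁ | r | t-test SE larger by | m (slope 0.5) | m (slope 1.0) | Bias in difference |
|---|---|---|---|---|---|
| 42% | 0.952 | 0.9% | 0.024 | 0.045 | 0.003 |
| 45% | 0.889 | 2.1% | 0.054 | 0.100 | 0.007 |
| 60% | 0.667 | 6.6% | 0.158 | 0.279 | 0.018 |
| 80% | 0.500 | 10.4% | 0.236 | 0.413 | 0.027 |

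With equal slopes and equal 1-month distributions the two m values coincide and the bias is zero. Simulation gave an SE penalty of about 0% to 11% over the same range of p₁.

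**5. Simulation at p₁ = 60%** (2,000 trials per row, 1,595 per arm, true difference 0.030):

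| Drop-out slope, control / TTS | t-test | Using the 1-month score |
|---|---|---|
| 0 / 0 | 0.0299 | 0.0297 |
| 0.5 / 0.5 | 0.0293 | 0.0301 |
| 1 / 1 | 0.0266 | 0.0294 |
| 0.5 / 1.0 | 0.0483 | 0.0303 |
| 1.0 / 0.5 | 0.0087 | 0.0302 |

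In the first row the SEs are 0.0142 and 0.0134. Since (0.0142/0.0134)² ≈ 1.12, using the 1-month score is worth about 12% more 12-month interviews.

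**6. When only the early outcome differs by arm.** In a second simulation everyone answers at 1 month, 40% answer at 12 months, and the slope is 1 in both arms. With an effect of 0.2 SD at 1 month and none at 12 months, the t-test bias was −0.014, −0.021 and −0.027 SD at correlations 0.4, 0.6 and 0.8. The type I error was 6.5%, 7.4% and 9.4%. On an SD of 0.25 these biases are about −0.004 to −0.007. With no effect at either visit and slope 0.5 in both arms, bias was about zero and type I error 4% to 5%.

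**The case against.** A reader might infer that the t-test is biased whenever drop-out depends on earlier answers, or that the later results are valid only if loss is unrelated to earlier health. Neither follows. Such drop-out shifts each arm's mean, but the shifts cancel in the difference when the dependence and the early outcome are the same in both arms. Even with slope 1 in both arms and a true effect, the shift was about 0.003, roughly a fifth of the SE of 0.0142.

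The large shifts need arm-specific dependence. The article does not state this, and its design makes it less likely: patients are not told of the specific intervention, data collection is the same in both groups, interviews are scripted, and up to five call attempts are made. It remains possible, because the intervention is meant to change how many patients leave with undetected injuries, and patients who report one are offered follow-up pathways.

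A reader might also infer three unlinked tests per outcome. The article does not say which visit is tested. If each is, the 1- and 6-month answers are used at their own visits, though still not in the 12-month result. Visit structure and missing-data handling may properly sit in an analysis plan that is not shown; the point here is only that the method actually stated does not suit these outcomes.

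The remedy has limits that stand. No baseline EQ-5D is listed, so patients never interviewed contribute nothing to the model either. Its near-zero bias in the simulations holds because drop-out was made to depend only on the observed 1-month score. The simulations used that score alone, without clustering, and not the full three-visit model. Work time lost was not simulated.

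**Conclusion.** The point holds as one of precision and robustness for two secondary outcomes. A later-visit t-test gives up roughly 0% to 11% in standard error, depending mainly on the unstated 1-month contact rate (42% to 80%, correlation 0.6). Bias in the arm difference is conditional. It is negligible with equal dependence and similar early outcomes. With slopes of 0.5 and 1.0 per SD and an SD of 0.25 it is about 0.003, 0.007, 0.018 and 0.027 at 42%, 45%, 60% and 80% reached at 1 month. At 60% that is 0.018/0.0142 ≈ 1.3 standard errors; at 42%, 0.003/0.0142 ≈ 0.2. All these figures ignore clustering. The binary primary outcome and the sample size are untouched. The change is worth making because it uses data already collected and needs a weaker missing-data assumption than the t-test.

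**What to change.** In the statistical analysis section, replace the t-test for EQ-5D-5L and work time lost with one likelihood-based mixed model for repeated measures: arm, visit, arm by visit, and a hospital random effect, including every patient with at least one interview. Report the arm difference at each visit, and name one visit as the headline. Because work time lost is a bounded proportion, use a model suited to that, or robust or bootstrap standard errors. Simple two-group comparisons need not become repeated-measures models for outcomes measured once; whether they should allow for hospital is a separate question.

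Cost: a sentence or two of text and slightly more analysis, with no new patients or data. The model relies on loss being missing at random given earlier interviews, and it does not help patients who are never interviewed. The report should therefore also give the share interviewed at each visit by arm.

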## Background

Missed injuries after multi-trauma are a significant health problem, affecting young to middle-aged adults (mainly men). Estimates of incidence are highly variable, but most likely between 1 to 5% of all trauma patients have missed injuries [1,2]. Missed injury is a common quality indicator in trauma care [3,4] and can be the result of several factors, including the prioritisation that takes place during the initial assessment in the Emergency Department (ED), quality of the assessor and institution-specific processes.

The standard primary and secondary surveys by ED, intensive care unit (ICU) and surgical teams have been shown to miss injuries [1,2,5,6]. Performance of a trauma tertiary survey (TTS) has been suggested as a tool to address this problem and minimise the risk of missed injuries. [5] The TTS should follow the episode of emergency care (primary and secondary survey and emergency interventions). It comprises a comprehensive general physical re-examination and review of all investigations, including diagnostic imaging and blood results, within 24 hours [6-8] and again when the patient is conscious, cooperative and mobilised. [5,8,9].

The TTS would be expected to reduce missed injuries and therefore improve trauma care. However, our recent systematic review [2] found sub-optimal evidence to support this.

Among the deficiencies was the substantial variation in outcome definitions for missed injury, leading to a recommendation for a classification (See Table 1). No study reported on missed injury rates after hospital discharge (Type III) or functional (long-term) outcomes. [5,7-14]

**Table 1 Tab1:** **Missed injury classification** [2]

**Missed injury Type: (delay of)**	**Description**
Type I ≤ 24 hours)	***Before trauma tertiary survey (TTS), or as result of TTS - in-hospital:***
	Injury missed at initial assessment (primary and secondary survey and emergency intervention), but detected within 24 hours, before or through formal TTS.
	(that is, injury missed at initial assessment)
Type II (>24 hours)	***After TTS, in-hospital:***
	Injury missed by TTS, detected in hospital after 24 hours.
	(that is, injury missed at initial assessment *and* TTS,)
Type III (After hospital discharge)	***After TTS, after hospital discharge:***
	Injury missed during hospital stay including TTS,
	(that is, injury missed at initial assessment *and* TTS *and* hospital stay)

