### Data collection

Data collection processes are the same for both Groups. The prospectively identified eligible patients will have their primary and secondary survey performed in the ED. All clinical reviews (including ward rounds) in the first 24 hours on the ward after surgical or interventional radiology intervention will be documented using a previously used [15,16] data collection tool (Additional file 2: Appendix B). Data will be collected by a trained research nurse will include demographic variables, mechanism of injury, Australasian Triage Scale category (ATS) [18] and Glasgow Coma Scale (GCS) on arrival in ED. The Injury Severity Score (ISS) [19] will be calculated after discharge. An ISS score of greater than 15 indicates severe trauma.

Data related to the inpatient admission will include whether a (formalised) TTS is documented during admission and which components of the TTS are performed. A list of injuries, newly detected injuries and changes in management will be collected. A central blinded panel of experts, comprised of at least two emergency physicians and 2 (trauma) surgeons, will class newly detected injuries in-hospital as Type I, Type II or not a new injury (see Table 2). A scripted follow-up telephone interview (Additional file 3: Appendix C) will be conducted at 1, 6 and 12 months after discharge. This follow-up interview will collect data on (Type III) missed injuries after discharge, complications of the injury (parasthaesia, chronic pain) or complications of care (postoperative infections and venous thrombo-embolism), return to pre-injury function, and a validated quality of life (QoL) questionnaire (EuroQoL EQ-5D-5 L [20]).

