### Outcome measures

The primary outcome is Type III missed (Post-hospital discharge) injury rate. This study aims to compare the effect of a formalised TTS compared to routine care on missed injury rates after hospital discharge (type III).

Secondary outcomes are:Maintenance of intervention effect (comparing two 12-month periods in Group 1)*During Hospital Stay*In-hospital missed injury rate (Type I and II combined)Proportion of TTS performedHospital bed days, ICU bed days*During Follow-up (1,6 and 12 months post hospital discharge)*Clinically significant missed injuries (as determined by expert panel)Interventions required for delayed diagnosis (Type I and II) or missed injuries (Type III)Diagnostic imaging usage (CT, MRI, USS)Predefined complications of care and injury (see above)Readmissions to hospitalDays off workQuality of life (EQ-5D-5 L)Days off workMortality

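### The crude chi-square stated for proportions, and so for the primary outcome, ignores hospital clustering and the arrival variables collected on every patient

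*Protocol article*

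**What the plan says.** The Outcome measures section states: "The primary outcome is Type III missed (Post-hospital discharge) injury rate". This is a proportion. For the comparison of proportions, the section Statistical analysis and sample size says that a "chi-square test will be used to compare differences in proportions", with an independent t-test for continuous variables. The article names no regression, covariate, hospital term or cluster-level analysis for the clinical outcomes. Patient characteristics enter only the health-economic sub-group and sensitivity analyses.

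The same section recognises clustering when it sizes the trial. It explains that variation between clusters requires a correction through the ICC, and it cites an average ICC of 0.01 for blunt trauma.

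Under Randomisation, hospitals are allocated 1:1 by a computer-generated random number function, with no stratification, matching or constraint stated. Under Data collection, the research nurse records "demographic variables, mechanism of injury, Australasian Triage Scale category (ATS) [18] and Glasgow Coma Scale (GCS) on arrival in ED". Table 2 also lists age and sex and says that one standard form is used for all patients.

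**The concern.** Two things follow from comparing arms with a crude chi-square when hospitals are the randomised units.

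First, the test treats patients as independent. Variation between hospitals is left out of its standard error, so confidence intervals are too narrow and the false-positive rate exceeds 5%. The t-test for continuous outcomes has the same fault.

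Second, neither test can take a covariate. With 8 hospitals per arm, the arms may differ by chance in age, mechanism of injury, triage category or arrival GCS. These are all fixed before any tertiary survey, and they plausibly bear on how easily an injury is missed. Such an imbalance would stay in the realised estimate although the data to adjust for it are already planned.

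At stake is whether a significant result can be believed. The Discussion section says that the findings will decide between wide implementation and abandonment.

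**Working it through.** **Inputs from the protocol.** Rates of 14% and 9%, alpha 0.05, power 0.80, 638 completers per group, 40% follow-up, 1,595 enrolled per arm, 16 hospitals (8 per arm) and ICC 0.01. Sidedness is not stated; a two-sided test reproduces the figure.

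**Step 1: the plan's own figure.** The protocol says: "Using an alpha of 0.05 and a power of 0.80, a sample size of 638 patients per group". With a mean rate of 0.115:

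n = [1.96 × √(2 × 0.115 × 0.885) + 0.8416 × √(0.14 × 0.86 + 0.09 × 0.91)]² / 0.05² = (0.8843 + 0.3786)² / 0.0025 ≈ 638.

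Then 638 / 0.40 = 1,595 per arm, or 3,190 in total. Both figures reproduce.

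**Step 2: design effect.** Enrolled per hospital: 1,595 / 8 ≈ 199. Completers per hospital: 199.4 × 0.40 ≈ 79.75. DEFF = 1 + (79.75 − 1) × 0.01 ≈ 1.79.

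**Step 3: true type I error of the chi-square.** 2 × [1 − Φ(1.96 / √1.79)] = 2 × [1 − Φ(1.466)] ≈ 14%. A beta-binomial simulation of 8 against 8 hospitals with 80 completers each gave 14.2%. The figure is 9.7% at ICC 0.005 and 22% at ICC 0.02. If all 199 enrolled patients per hospital were analysed, it would be about 26% at ICC 0.01.

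**Step 4: the same result in percentage points.**
- Between-hospital SD: √(0.01 × 0.115 × 0.885) ≈ 3.2 points.
- SD that this adds to the arm difference: 3.2 × √(2/8) ≈ 1.6 points.
- Binomial sampling SD: √(2 × 0.115 × 0.885 / 638) ≈ 1.8 points.
- Combined: √(1.6² + 1.8²) ≈ 2.4 points.

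The chi-square counts only the 1.8, against a target effect of 5 points. If case mix explained half of the between-hospital variance (an assumption), its share of the arm-difference SD would be 1.6 × √0.5 ≈ 1.1 points.

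**Step 5: what covariates might add to a cluster-valid test.** The document gives no covariate-outcome correlation, so the first column below is assumed. Power = Φ(0.05 / SE − 1.96), with SE² = (0.1204 + 0.0819) / 638 × DEFF. ICC 0.01 is reduced by the share explained.

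| Between-hospital variance explained | Residual ICC | DEFF | Power (normal) | Power (t, 14 df) |
|---|---|---|---|---|
| 0% | 0.0100 | 1.79 | 56% | 50% |
| 25% | 0.0075 | 1.59 | 61% | 55% |
| 50% | 0.0050 | 1.39 | 66% | 60% |
| 75% | 0.0025 | 1.20 | 73% | 67% |

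If the covariates explained 10% of within-hospital variance and none between hospitals, power would rise by only about 2 points.

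**Step 6: covariates without a hospital term do not cure the test.** Repeating step 3 with the residual ICCs, type I error would still be about 12%, 10% and 7% at 25%, 50% and 75% explained. Explaining within-hospital variance only would leave it at 14% to 15%.

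**The case against.** The strongest reply is that covariate choice is commonly left to an analysis plan. An unadjusted comparison in a randomised trial is also valid if its standard error is right, and the article's sentence on tests is generic and does not forbid adjustment. That much stands: lack of adjustment alone would not be an error. It does not rescue the test, because the article states the chi-square as the method, names no other for proportions, and so fixes a standard error that omits clustering.

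A second reply is that nothing shows arrival variables to explain differences between hospitals. The Background section attributes missed injury to several factors, "including the prioritisation that takes place during the initial assessment in the Emergency Department (ED), quality of the assessor and institution-specific processes", and assessor quality and local process are not removed by adjusting for age or GCS. This also stands, and it is why the precision gain is given only as a range of assumptions.

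A reader might infer more than the document supports:
- **That the effect estimate is biased.** Hospitals are randomised, so the estimate is unbiased in expectation; the issue is chance imbalance.
- **That the planned chi-square has 56% power.** That figure belongs to a cluster-corrected test that the article does not state. On the same inputs the chi-square would reject about 74% of the time, Φ((2.81 − 1.96) / 1.34), but only because its threshold is too lenient.
- **That the plan adjusts for a post-treatment severity score.** It says "The Injury Severity Score (ISS) [19] will be calculated after discharge", but nowhere proposes ISS as a covariate.
- **That low follow-up makes the chi-square wrong.** The earlier study "achieved a telephone follow-up rate of 40% at 6 months", which the protocol extrapolates to 12 months. Differences between those reached in each arm are a missing-data question, not a fault of this test.

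**Conclusion.** The point holds. The only test stated for the primary outcome ignores the clustering that the sample-size text acknowledges and makes no use of arrival variables that will be available for every patient.

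The firm part is the standard error: a type I error of about 14% instead of 5%. This rests on ICC 0.01, equal hospitals and about 80 completers each, and it ranges from about 10% to 22% for ICCs of 0.005 to 0.02.

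The softer part is adjustment. It would reduce the influence of chance case-mix imbalance among 16 hospitals and may recover some power. The step from 56% to between 61% and 73% depends wholly on assumed shares of explained variance, and the gain could be close to nil. Adjustment is therefore a worthwhile improvement to make together with the cluster correction, not a substitute for it.

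**What to change.** Replace the chi-square as the primary comparison with a patient-level regression that includes a hospital term (mixed model or GEE) and a small-sample correction suited to about 16 clusters. Adjust for a short, prespecified list of arrival variables, such as age, mechanism of injury, ATS category and arrival GCS. Report the adjusted risk difference with a 95% confidence interval, and give an unadjusted but cluster-valid result as a sensitivity analysis. Apply the same structure to continuous outcomes in place of the t-test.

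If a severity covariate is wanted, do not use an ISS that counts injuries found after the ED surveys, because the intervention can change it. Score it only from injuries known at the end of the primary and secondary survey.

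The cost is a change of wording and modest analysis work, with no new variables to collect. The article reports that recruitment had not begun, so the change can be made before any data exist. The main constraint is that 16 clusters call for few covariates, and categorical ones such as mechanism and ATS may need to be grouped.
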